## Abstract

**Background:**

Patients with advanced stage non-small cell lung cancer (NSCLC) or small cell lung cancer (SCLC) often experience multidimensional impairments, affecting quality of life during their course of disease. In lung cancer patients with operable disease, several studies have shown that exercise has a positive impact on quality of life and physical functioning. There is limited evidence regarding efficacy for advanced lung cancer patients undergoing palliative treatment. Therefore, the POSITIVE study aims to evaluate the benefit of a 24-week exercise intervention during palliative treatment in a randomized controlled setting.

**Methods/design:**

The POSITIVE study is a randomized, controlled trial investigating the effects of a 24-week exercise intervention during palliative treatment on quality of life, physical performance and immune function in advanced, non-operable lung cancer patients. 250 patients will be recruited in the Clinic for Thoracic Diseases in Heidelberg, enrolment begun in November 2013. Main inclusion criterion is histologically confirmed NSCLC (stage IIIa, IIIb, IV) or SCLC (Limited Disease-SCLC, Extensive Disease-SCLC) not amenable to surgery. Patients are randomized into two groups. Both groups receive weekly care management phone calls (CMPCs) with the goal to assess symptoms and side effects. Additionally, one group receives a combined resistance and endurance training (3x/week). Primary endpoints are quality of life assessed by the Functional Assessment of Cancer Therapy for patients with lung cancer (FACT-L, subcategory Physical Well-Being) and General Fatigue measured by the Multidimensional Fatigue Inventory (MFI-20). Secondary endpoints are physical performance (maximal voluntary isometric contraction, 6-min walk distance), psychosocial (depression and anxiety) and immunological parameters and overall survival.

**Discussion:**

The aim of the POSITIVE trial is the evaluation of effects of a 24-week structured and guided exercise intervention during palliative treatment stages. Analysis of various outcomes (such as quality of life, physical performance, self-efficacy, psychosocial and immunological parameters) will contribute to a better understanding of the potential of exercise in advanced lung cancer patients. In contrast to other studies with advanced oncological patients the POSITIVE trial provides weekly phone calls to support patients both in the intervention and control group and to segregate the impact of physical activity on quality of life.

**Trial registration:**

ClinicalTrials.gov NCT02055508 (Date: December 12, 2013)

## Background

Worldwide, lung cancer is one of the most commonly diagnosed cancer types and also the leading cause of death in males [1]. Lung cancer incidence rates are highest in Europe and Northern America [2] and lung cancer belongs to the most aggressive human cancers with a 5 year survival rate of 10-15 % [3]. For patients with metastatic disease, 5 year overall survival is 2 % [4].

Advanced lung cancer patients often experience multidimensional impairments affecting quality of life during their course of disease [5]. Impairments result from symptoms of the disease and comorbidities on the one hand and side effects of treatment on the other hand. Moreover, socioeconomic problems arise and patients lose their social and professional integration. They are facing physical fragility and in many cases end-of-life situations [6]. A study in a representative sample of advanced cancer patients (*n* = 1630) in Denmark observed that lung cancer patients had exacerbated symptom burden (e.g. fatigue, dyspnea, pain, appetite loss), and presented with reduced physical and emotional function and quality of life, when compared with other cancer diagnoses like head and neck, gynecological, prostate, breast, gastrointestinal or bladder tumors [5]. Other investigations showed that patients with advanced lung cancer have specific problems such as coughing, shortness of breath, anorexia, and insomnia that need to be addressed [7–10].

Numerous studies have shown that physical activity positively affects quality of life, physical capacity and fatigue in cancer patients, irrespective of the tumor type [11–13]. Specifically for lung cancer patients, exercise studies in the pre-and post-operative setting showed an improvement in physical performance and cardiorespiratory fitness [14–18].

In contrast, studies investigating the effects of physical exercise in non-operable patients with advanced lung cancer are rare. The number of randomized controlled trials is limited and current knowledge is derived from feasibility and observational studies [19–23].

Previous investigations from our team with 39 lung cancer patients (POSITIVE study, Part I) assessed physical and psychological performance including dynamometry, 6-min walk tests and standardized questionnaires. As expected the results showed that advanced lung cancer patients experience muscular weakness, especially in the lower extremities, lower endurance performance and decreased quality of life compared to a healthy reference group [24].

In a subsequent feasibility study (POSITIVE study, Part II) our team observed favorable effects of physical exercise on the psychosocial performance and physical status of patients with advanced NSCLC that are now evaluated in the here described randomized controlled trial [24].

In addition to the benefits of physical training for quality of life, physical capacity and fatigue there is accumulating evidence that exercise can also modulate the immune system [25–36]. It is well known that the balance of specific effector T cells and immune suppressive regulatory T cells is essential for a healthy immune system and their imbalance can result of autoimmune diseases [37]. Thus, the interplay of established tumor specific effector and regulatory T cell populations might impact tumor progression, response to chemotherapy and patient prognosis [38–40]. Yet, there is little known about the effects of exercise on tumor specific adaptive immune modulation. Therefore, the scope of Positive III also includes the analysis of effects of exercise on biomarkers of immune function in cancer patients.

In conclusion, exercise provides beneficial effects in cancer patients overall [12, 41, 42]. Furthermore, there is strong evidence for physical exercise reducing cancer-related fatigue [43] and some evidence from a limited number of studies that exercise has beneficial effects on quality of life in advanced lung cancer patients. Possible pathways of how exercise may influence relevant lung cancer outcomes have not yet been studied. Therefore, the POSITIVE study (Part III) aims to investigate the benefits of a 24-week exercise intervention program in a randomized controlled setting. A translational program on immunological pathways will evaluate the potential relation between exercise-driven immunological changes and the influence on tumor specific T cell response. In contrast to other published studies, the POSITIVE study (Part III) is designed to isolate the specific impact of a 24-week exercise intervention on quality of life beyond social contact by providing social support to each study participant via weekly care management phone calls (CMPC).

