## Methods and Design

### Study design

The POSITIVE study (Part III) is a randomized, controlled exercise intervention trial including patients with histologically confirmed NSCLC (stage IIIa, IIIb or IV) or SCLC (LD-SCLC, ED-SCLC), not amenable to surgery. Enrolment of patients started in November 2013, with an estimated recruitment period of approximately two and a half years. Inclusion and exclusion criteria are presented in Table 1.

**Table 1 Tab1:** Inclusion and exclusion criteria. Inclusion and exclusion criteria of the POSITIVE study (Part III)

Inclusion criteria	Exclusion criteria
• NSCLC, histologically confirmed stage IIIB/IV • Receiving systemic, palliative treatment • Age ≥18 years • BMI >18 kg/m^2^ • ECOG performance status ≤2 • Signed informed consent	• Bone metastasis inducing skeletal fragility • Serious active infection • Inability to walk • Immobility (more than two days) • Previously untreated (non-irradiated or non-resected) symptomatic brain metastases • Severe neurologic or cardiac impairment • Severe respiratory insufficiency • Uncontrolled pain • Abuse of alcohol or drugs reducing compliance to the study • Any circumstance that would impede ability to give informed consent or adherence to study requirements

The study will enroll 250 patients (*n* = 125 in each arm) (Study design, Fig. 1). The first arm encompasses an “Exercise Intervention Program (EIP) and Care Management Phone Calls (CMPC)”, whereas the second arm contains “Care Management Phone Calls (CMPC)” alone. Outcome measures are assessed at baseline (T0), after 12 weeks (T1), after 24 weeks (T2) and thereafter at 9 months (T3) and 12 months (T4). The maximum study duration per patient is 1 year. The study protocol for the POSITIVE study (Part III) has been reviewed and approved by the ethics committee of the Medical Faculty of Heidelberg (S-326/2013) in November 2013.

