Exercise training is scheduled 3 times a week. The intensity of the endurance training sessions is 70-85 % of estimated maximum heart rate. Depending on patients’ individual endurance capacity, training starts at a duration of at least 15 min with subsequent increases to 45 min. Training duration and intensity for the home-based sessions is tailored using the RPE (Rate of Perceived Exertion) scale (Borg) and a well-established self-rating procedure from our lung cancer feasibility and allogeneic transplant study [44, 45]. Specifically, at the beginning of each training session patients are asked to complete an assessment of pain, fatigue, emotional status, and distress. This assessment is used to self-rate patients’ well-being and group them into 3 different categories, represented by the traffic light colors red, yellow and green, for tailoring the exercise intervention. Depending on subjectively rated well-being, the patient performs higher or lower intensity training. After each training session patients are asked to document their training in a training log. The supervised training sessions in the local outpatient training center include resistance exercise on machines and endurance training on an ergometer/treadmill. In the outpatient setting, patients and exercise specialists in cooperating training centers are instructed accordingly. During the first 12 weeks of the intervention program, supervised training sessions are conducted twice a week with an additional self-administered home-based training once a week. With the beginning of week 13 supervised training in cooperation training centers is reduced to 1x/week and patients are instructed to perform two home-based training sessions per week.

Supervised resistance and endurance training protocols comply with the American College of Sports Medicine (ACSM) exercise guidelines for cancer survivors [46] and with ACSM recommendations for progressive resistance training for novice weightlifters and older adults for one to three sets at a weight that can be done/lifted for 8 to 12 repetitions (approximately 60–80 % of 1-RM) [47, 48].

On the basis of the CMPCs the study nurse regularly reviews exercise adherence and identifies barriers and problems with regard to exercise. Exercise sessions are temporarily interrupted if pain, dizziness, or other contraindications (infections with body temperature ≥38 °C, impaired hematopoietic capacity) occur.

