Other currently ongoing studies that focus on the effects of exercise in advanced lung cancer patients might also help to generate important information about the most feasible way to improve quality of life and physical performance in this patient population [67, 70].

The ongoing POSITIVE study (Part III) enrolls only advanced, non-operable patients. The major difference to previous and ongoing studies is the inclusion of the CMPCs in the control arm. The American Society of Clinical Oncology Statement recommends an individualized care for patients with advanced cancer [73] because physical discomfort is recognized earlier and treatment could be adapted. The phone calls offer the possibility of a continuous monitoring and continuous social contact. Previous studies with metastatic cancer patients did not offer supportive strategies to this extent. Therefore, the CMPCs are an important characteristic of the POSITIVE study (Part III). Patients are called and interviewed weekly via a standardized questionnaire. On the basis of the weekly phone calls symptoms and discomfort are recognized earlier and can be managed properly. The weekly phone calls might also improve the psychosocial well-being of the patients in general [74]. These potential contacts could improve awareness to symptoms and side effects as well as facilitate coping strategies. The phone calls are provided to all patients in the study to isolate the actual effect of the exercise intervention on this dimension.

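### The trial is said to isolate exercise from social contact, but only the phone calls are matched: the exercise arm has 24 planned supervised sessions by T1 and the control arm none

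*Protocol article*

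**What the plan says.** The end of the Background states that the trial is "designed to isolate the specific impact of a 24-week exercise intervention on quality of life beyond social contact", and gives the means: "by providing social support to each study participant via weekly care management phone calls (CMPC"). The Discussion paragraph of the Abstract makes the same point, presenting the calls in both arms as the way to separate out what physical activity does to quality of life. The main Discussion says "The phone calls are provided to all patients in the study to isolate the actual effect of the exercise intervention on this dimension", and names the calls in the control arm as the major difference from previous and ongoing studies.

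Study design defines the first arm as the exercise programme plus the calls, "whereas the second arm contains “Care Management Phone Calls (CMPC)” alone".

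The Interventions section then describes what the exercise arm receives:

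- "Exercise training is scheduled 3 times a week".
- In the first 12 weeks, "supervised training sessions are conducted twice a week with an additional self-administered home-based training once a week".
- From week 13, "supervised training in cooperation training centers is reduced to 1x/week and patients are instructed to perform two home-based training sessions per week".
- A physiotherapist or sports scientist instructs patients individually in the home exercises.
- "On the basis of the CMPCs the study nurse regularly reviews exercise adherence and identifies barriers and problems with regard to exercise".

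No section describes a counterpart to these contacts for controls, and none lists the difference as a limitation.

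**The concern.** Giving both arms the same calls removes the effect of the calls from the comparison. It does not remove the effect of social contact in general, because one arm also regularly meets exercise staff in person and the other does not. The claim made in three places is the wider one.

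The article's own reasoning shows why this matters. The Discussion accepts that weekly calls might improve psychosocial well-being and that such contact could help symptom awareness and coping. If telephone contact can plausibly move these outcomes enough to need balancing, so can regular in-person sessions. The two primary endpoints, FACT-L physical well-being and MFI general fatigue, are questionnaires completed by patients who necessarily know whether they are in the training arm.

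At stake is the interpretation of a positive result. The article presents the separation of exercise from contact as what sets this trial apart, and readers would take a significant difference as evidence about exercise itself.

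**Working it through.** **1. The plan's own training frequency.** Inputs are the session numbers in Interventions.

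| Period | Supervised per week | Home per week | Total per week |
|---|---|---|---|
| Weeks 1–12 | 2 | 1 | 3 |
| Weeks 13–24 | 1 | 2 | 3 |

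Both rows agree with the stated three sessions a week. Over 24 weeks the total is 3 × 24 = 72.

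**2. Planned supervised sessions by arm.**

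- By T1 (12 weeks, the time point of the primary model in Data analysis): 12 × 2 = 24 in the exercise arm, 0 in the control arm.
- Over 24 weeks: 12 × 2 + 12 × 1 = 36 in the exercise arm, 0 in the control arm.
- Home sessions: 12 × 1 + 12 × 2 = 36, and 36 + 36 = 72 as above.

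These are planned sessions, assuming that training starts at randomisation. Attended numbers will be lower with missed sessions and dropout.

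**3. Stated property against described arms.**

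| Component | Exercise arm | Control arm | Matched? |
|---|---|---|---|
| Weekly symptom calls | yes | yes | yes |
| Supervised in-person sessions by T1 | 24 | 0 | no |
| Individual instruction by exercise staff | yes | none described | no |
| Nurse review of adherence and barriers | yes | none described | no |

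Isolation from social contact would need contact to be comparable in the arms apart from the exercise. Only the first row meets that condition.

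**4. What an unmatched contact effect could do (illustration only).** The documents give no size for a contact effect, so a range is assumed: a shift of 0.1 to 0.4 SD from contact alone, with no effect of exercise itself. Other inputs are 75 evaluable patients per group and nominal alpha 2.5 % (taken as two-sided, since sidedness is not stated). The correlation ρ between T0 and T1 is not given. It is solved from the stated power at e = 0.4, reading e in SD units, and is not independently verified:

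(z₀.₉₈₇₅ + z_power) × √(2/75) / 0.4 = 1/√(1 − ρ²)

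- MFI, power 72.0 %: (2.241 + 0.583) × 0.1633 / 0.4 = 1.153, so ρ ≈ 0.50.
- Physical well-being, power 80.9 %: (2.241 + 0.874) × 0.1633 / 0.4 = 1.272, so ρ ≈ 0.62.

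The chance of a significant result favouring the exercise arm is Φ(δ / [√(1 − ρ²) × √(2/75)] − 2.241):

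| Assumed contact shift δ | MFI | Physical well-being |
|---|---|---|
| 0.1 SD | 6 % | 7 % |
| 0.2 SD | 20 % | 25 % |
| 0.3 SD | 45 % | 54 % |
| 0.4 SD | 72 % | 81 % |

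The last row returns the stated powers by construction. The table shows only that the test cannot tell a contact effect from an exercise effect of the same size. It is not evidence that such an effect exists.

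**The case against.** The strongest reply is that the Background sentence states its own means, the calls, and contrasts this trial with others. The Discussion ties the isolating role of the calls to psychosocial well-being. On that reading the claim is only that the effect of the calls drops out of the comparison, which calls in both arms largely achieve. Study design also states the contrast openly, supervision is part of the exercise programme by definition, and Objectives claims nothing about mechanism.

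Much of this stands. The contrast is described openly and the randomised comparison of it is sound. The narrow reading does not fit the text, however: the Background speaks of social contact, not of the calls, and nothing limits that wording.

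Several stronger readings are tempting and are not supported:

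- **That the exercise arm is coached by telephone, or gets longer calls.** The text says only that the nurse reviews adherence and identifies barriers on the basis of the calls. It gives no call length, and it describes a symptom scale and standardised questionnaire common to all patients.
- **That total contact differs by a stated multiple.** Adding calls and training sessions treats unlike things as equal. Table 2 says only that calls are weekly and no end date is given, so a 24-week count of calls would be an assumption.
- **That a positive result would say nothing about exercise.** Strength and walk tests in both arms, and exercise logs in the exercise arm, give supporting evidence on whether training had a physical effect. Attribution would be incomplete rather than impossible, because these measures do not show how much of a change in self-reported well-being or fatigue came from training.
- **That the calls should be re-scripted.** The symptom scale used in the calls is listed under other assessments in Table 2 and is not an endpoint. Reordering the questions would therefore not protect the two primary questionnaires, and it would leave the supervised sessions unmatched. Moving the adherence questions to a separate contact would add to the imbalance.

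**Conclusion.** The point holds as one of interpretation. The design matches telephone contact but not in-person contact, which differs by 24 planned supervised sessions to none at the primary time point and by 36 to none over the programme. The stated property of isolating exercise beyond social contact is therefore absent.

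The comparison of exercise programme plus calls with calls alone remains a valid randomised contrast. The hypotheses, alpha, sample size of 250 and stated power do not change. What cannot be done is to separate a difference in the two self-reported primary endpoints from the extra contact that came with training.

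The session counts rest only on the schedule in Interventions. The size of any contact effect is unknown from the documents. A reader might infer that the trial is biased or needs an attention-matched control arm. The documents do not show the first, and the second is a design preference that correcting the claim does not require.

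**What to change.** In the Discussion paragraph of the Abstract, at the end of the Background and in the main Discussion, replace the isolation claim with wording such as: the trial estimates the effect of the exercise programme, including its in-person supervision and contact, over and above weekly telephone symptom management.

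Add one sentence to the Discussion stating that in-person sessions, individual instruction and the adherence review have no counterpart in the control arm, and that this limits attribution of any effect to exercise itself. Carry the same wording into the results report.

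The cost is a few sentences and a narrower mechanistic claim. No change to conduct, staffing, sample size or analysis is needed, so the correction can be made although enrolment began in November 2013.

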## Methods and Design

### Study design

The POSITIVE study (Part III) is a randomized, controlled exercise intervention trial including patients with histologically confirmed NSCLC (stage IIIa, IIIb or IV) or SCLC (LD-SCLC, ED-SCLC), not amenable to surgery. Enrolment of patients started in November 2013, with an estimated recruitment period of approximately two and a half years. Inclusion and exclusion criteria are presented in Table 1.

**Table 1 Tab1:** Inclusion and exclusion criteria. Inclusion and exclusion criteria of the POSITIVE study (Part III)

Inclusion criteria	Exclusion criteria
• NSCLC, histologically confirmed stage IIIB/IV • Receiving systemic, palliative treatment • Age ≥18 years • BMI >18 kg/m^2^ • ECOG performance status ≤2 • Signed informed consent	• Bone metastasis inducing skeletal fragility • Serious active infection • Inability to walk • Immobility (more than two days) • Previously untreated (non-irradiated or non-resected) symptomatic brain metastases • Severe neurologic or cardiac impairment • Severe respiratory insufficiency • Uncontrolled pain • Abuse of alcohol or drugs reducing compliance to the study • Any circumstance that would impede ability to give informed consent or adherence to study requirements

The study will enroll 250 patients (*n* = 125 in each arm) (Study design, Fig. 1). The first arm encompasses an “Exercise Intervention Program (EIP) and Care Management Phone Calls (CMPC)”, whereas the second arm contains “Care Management Phone Calls (CMPC)” alone. Outcome measures are assessed at baseline (T0), after 12 weeks (T1), after 24 weeks (T2) and thereafter at 9 months (T3) and 12 months (T4). The maximum study duration per patient is 1 year. The study protocol for the POSITIVE study (Part III) has been reviewed and approved by the ethics committee of the Medical Faculty of Heidelberg (S-326/2013) in November 2013.

